## Abstract

**Background:**

Musculoskeletal disorders, including chronic back pain, osteoarthritis, rheumatoid arthritis, and fibromyalgia, are leading causes of chronic pain and reduced quality of life. Standard treatment approaches often focus on physical symptoms, while psychosomatic factors are sometimes overlooked. This study aims to evaluate the effectiveness of adjunct psychosomatic interventions—guided meditation and aromatherapy—on pain perception, stress levels, and quality of life in patients with musculoskeletal disorders.

**Methods:**

This is a three-arm, prospective, randomized controlled trial conducted in Germany. A total of 90 participants aged 18 to 90 with chronic musculoskeletal disorders will be randomized into one of three groups: (1) guided meditation, (2) aromatherapy, or (3) control receiving standard care. The intervention groups will receive either body-scan meditation (23 min, twice weekly) or aromatherapy (5–10 min daily) for one week. The primary outcomes include pain intensity (measured using the Numerical Rating Scale), perceived stress (measured using the Perceived Stress Questionnaire), and quality of life (measured using the EQ-5D). Secondary outcomes will include pain medication consumption. Follow-up assessments will be conducted at 3-, 6-, and 12-month post-intervention. Data will be analyzed using an intention-to-treat approach with ANCOVA for primary endpoints.

**Discussion:**

This trial will provide valuable insights into the effectiveness of psychosomatic interventions as adjunct therapies for managing chronic pain and stress in musculoskeletal disorders. If successful, these interventions could be implemented as cost-effective and non-invasive strategies to improve quality of life and pain management for patients with musculoskeletal conditions. The findings may also inform future studies on integrative treatment approaches for chronic pain conditions.

**Trial registration:**

The trial is registered at the German Clinical Trials Register (https://www.drks.de), registration number DRKS00034506.

## Introduction

### Background and rationale {6a}

Musculoskeletal disorders (MSDs) are among the most prevalent chronic conditions globally, significantly impacting pain, stress levels, and quality of life [1, 2]. Conditions such as chronic back pain, osteoarthritis, rheumatoid arthritis, and fibromyalgia are common MSDs that frequently lead to persistent discomfort and functional limitations. Despite advances in conventional medical treatments, many patients with these conditions continue to experience considerable pain and reduced quality of life, prompting a search for additional therapeutic options [3, 4].

Integrative therapies, including psychosomatic approaches, have gained attention as potential adjuncts to conventional treatments for managing chronic pain and stress. Psychosomatic therapies often encompass techniques aimed at enhancing the mind-body connection, which may offer benefits beyond those achieved through standard medical care alone. Interventions such as guided meditation and aromatherapy are designed to promote relaxation, reduce stress, and potentially mitigate pain through non-pharmacological means [5].

Guided meditation, for instance, is a practice that involves directing the participant’s attention to various parts of the body, fostering a state of mindful awareness and relaxation. This approach has shown promise in improving pain management and emotional well-being in various patient populations [6, 7]. Similarly, aromatherapy, which utilizes the inhalation of essential oils, is believed to exert calming effects on the nervous system and could serve as a complementary method for pain and stress relief [8, 9].

This study aims to explore the effects of these complementary psychosomatic therapies on pain, stress, and quality of life in patients with musculoskeletal disorders. By conducting a prospective, three-arm, randomized controlled trial, we will evaluate the effectiveness of guided meditation and aromatherapy compared to standard care. This research seeks to determine whether these integrative approaches can provide meaningful benefits to patients suffering from chronic musculoskeletal conditions. Thus, it is hypothesized that providing patients with easy-to-implement methods for self-regulation, stress management, and anxiety reduction will result in a clinically relevant increase in quality of life scores, reduced pain levels, and fewer limitations in performing daily tasks.

Despite increasing interest in integrative and psychosomatic approaches, several important research gaps remain. Current standard care for musculoskeletal disorders primarily focuses on pharmacological treatment, physiotherapy, and surgical approaches. While effective for many patients, these strategies often insufficiently address the psychological and stress-related contributors to chronic pain. Furthermore, non-pharmacological interventions such as meditation and aromatherapy are widely used in clinical practice but lack standardized implementation protocols and high-quality randomized controlled trials specifically targeting heterogeneous musculoskeletal populations. Existing studies are frequently limited by small sample sizes, short follow-up periods, and single-intervention designs [10, 11]. Therefore, a rigorously designed randomized controlled trial evaluating standardized psychosomatic adjunct therapies is needed to address this gap.

### Objectives {7}

The objective of this trial is to examine the effect of adjunct psychosomatic therapies on pain perception, stress, and quality of life in patients with (i) lower back pain, (ii) osteoarthritis, (iii) rheumatoid arthritis, and (iv) fibromyalgia.

Specifically, we aim to:Evaluate the reduction in perceived pain using the Numerical Rating Scale (NRS).Assess changes in stress levels using the Perceived Stress Questionnaire (PSQ).Examine improvements in quality of life with the EQ-5D questionnaire.

## Methods: participants, interventions, and outcomes

### Trial design {8}

This is a prospective, parallel three-arm randomized controlled trial (Fig. 1).

**Fig. 1 Fig1:**
[figure not shown]
Schematic overview of the trial flow

### Study setting {9}

The study will be carried out in four physiotherapy practices in Germany (REHA SÜD 79115 Freiburg, TheraVita GmbH 79111 Freiburg, Physiotherapie Gundelfingen GbR 79194 Gundelfingen, Körperwer 79098 Freiburg).

### Eligibility criteria {10}

#### Screening and diagnosis

Eligible participants will be screened using medical records, clinical examination, and confirmation of diagnosis by the treating physician.

### Diagnostic criteria

Chronic lower back pain: pain ≥ 3 months confirmed by clinical assessment and imaging if availableOsteoarthritis: diagnosis according to ACR criteria and/or radiographic evidence [12]Rheumatoid arthritis: diagnosis according to ACR/EULAR classification criteria [13]Fibromyalgia: diagnosis according to ACR 2016 criteria [14]

#### Inclusion criteria

Age ≥ 18 yearsConfirmed diagnosis of one of the above musculoskeletal disorders Chronic pain duration ≥ 3 monthsStable medical treatment for ≥ 4 weeksAbility to provide informed consent

#### Exclusion criteria

Severe psychiatric disorders (psychosis, severe depression requiring hospitalization)Severe neurological diseasePregnancy or breastfeedingParticipation in another clinical trialCurrent use of structured mind–body interventions (yoga, meditation programs, relaxation therapy)

#### Washout requirements

NSAIDs: minimum 7-day washout before baseline assessmentComplementary therapies (e.g., yoga, meditation, relaxation programs): discontinued ≥ 2 weeks before enrollment 

### Drop-outs

Participants who withdraw consent or are lost to follow-up will be documented and included in intention-to-treat analyses.

### Who will take informed consent? {26a}

Participants will be approached in the physical therapy practice and given a verbal explanation of the study by a study researcher. A written participant information and consent form will be provided. Participants will be informed that their decision whether or not to participate in the study will not impact their access to routine care and that they can discontinue the participation in the study at any time. Participants will be given the opportunity to read, discuss, and ask questions. Those willing to participate will sign the consent form.

### Patient and public involvement

Patient representatives will be recruited through local patient advocacy groups and outpatient clinics using purposive sampling to ensure representation of the major diagnostic groups included in the trial. Patient representatives will be involved in the sense of participatory research [15, 16] in the conceptualisation of the study. These will participate during the whole research process. Further, focus group discussions will be held twice at University Hospital Regensburg, first to present the research strategy and preliminary results as well as to evaluate whether additional endpoints are of interest from the patient’s perspective. Second, it will be evaluated how patient-oriented, complementary treatment concepts can be established in daily clinical practice and medical aftercare. Regular meetings with the project partners will take place every 3 months.

### Additional consent provisions for collection and use of participant data and biological specimens {26b}

Additional written consent will be obtained for the collection and storage of blood samples for biomarker analysis (serum cortisol, C-reactive protein, and interleukin-6). Samples will be pseudonymized and stored according to institutional biobank regulations.

### Interventions

#### Explanation for the choice of comparators {6b}

In this study, two adjunct psychosomatic interventions—guided meditation and aromatherapy—will be compared to a control group receiving standard care as per current clinical guidelines. The choice of these comparators is based on the following rationale:

Guided meditation: This intervention involves a body-scan meditation that directs the participant’s focus on various body regions to promote mindfulness and relaxation. Guided meditation has been selected as it is a non-invasive technique widely used in psychosomatic medicine to reduce stress, alleviate pain, and enhance overall well-being [17–19]. The 23-min body-scan meditation, conducted twice weekly for 4 weeks, will be compared to standard care to evaluate its specific effects on pain perception, stress, and quality of life in patients with musculoskeletal disorders. The meditation protocol is based on standardized body-scan techniques derived from Mindfulness-Based Stress Reduction (MBSR).

Aromatherapy: Aromatherapy using fragrance sticks provides a simple, accessible intervention that could influence pain perception and stress reduction. It has been shown in some studies to have calming effects and improve emotional well-being, making it a suitable adjunct treatment [20, 21]. Participants will be instructed to use the fragrance sticks for 5–10 min daily for 1 week. The effects of this intervention will be compared to standard care to assess whether it offers additional benefits in managing chronic pain and stress. The fragrance sticks contain diluted essential oils compliant with EU cosmetic safety regulations. Participants will be screened for allergies and instructed to discontinue use in case of adverse reactions.

Control group (standard care): The control group will receive standard treatment based on clinical guidelines for managing musculoskeletal disorders. This includes routine medical care, physical therapy, and pain management protocols as applicable. The inclusion of a standard care group allows us to evaluate the added value of the psychosomatic interventions (meditation and aromatherapy) beyond conventional treatments. Standard care will follow national clinical guidelines and will be documented using a standardized checklist to ensure comparable treatment across centers.

### Intervention description {11a}

#### Group 1: Guided meditation

Participants will engage in a guided body-scan meditation, available through an online platform (https://www.tk.de/techniker/gesundheit-foerdern/stress-entspannung/aktiv-entspannen/body-scan-download-2007110, accessed 17.02.26) or via USB sticks/CDs. The meditation directs the participant’s attention to different body regions to raise awareness of bodily sensations and promote relaxation. Sessions will be conducted twice weekly for 23 min over 4 weeks.

#### Group 2: Aromatherapy

Participants will receive fragrance sticks for daily use (5–10 min per day). The participants will be instructed to use the sticks and provided with educational material on the therapeutic benefits of aromatherapy.

#### Group 3: Control (standard of care)

The control group will receive standard care as per existing clinical guidelines.

### Criteria for discontinuing or modifying allocated interventions {11b}

for the individual patients: As guaranteed in the patient information sheet previously to study inclusion, the individual patient will be excluded from study participation, if the patient withdraws his informed consent due to any reasons.for participating centers: Recruitment and data assessment of the follow-up examinations will be monitored by the Data Safety and Monitoring Board throughout the entire trial period. For recruitment of study patients, we have defined milestones at different time-points. If recruitment at the 50% landmark is below 20% of the total targeted number of patients, the enrolling center will have to be excluded from participating in the trial.for the whole trial: If recruitment is not achievable in more than one center, an interim analysis of the achieved effect size and subsequent reanalyses of the required sample size will reveal whether continuation of the trial is still realistic.

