### Sample size {14}

Assumptions: To determine the required sample size, we based our assumptions on previous studies investigating similar psychosomatic interventions in patients with chronic pain conditions. We assume the following for the primary outcome (pain reduction):

Effect size: A medium effect size of 0.5 is expected between the intervention groups and the control group.

Significance level (*α*): A two-sided significance level of 0.05 will be used.

Power (1-*β*): To detect a clinically meaningful difference, we aim for a statistical power of 80% (*β* = 0.2).

Drop-out rate: We anticipate a drop-out rate of 15% during the follow-up period.

Sample Size Calculation:

Using these assumptions, we calculated the required sample size using G*Power software for analysis of covariance (ANCOVA), with baseline pain scores as a covariate:

Minimum required participants per group: 30 participants in each group (guided meditation, aromatherapy, and control) are required to detect a medium effect size with 80% power at a significance level of 0.05.

Total sample size: Accounting for a 15% drop-out rate, the total number of participants to be recruited is 104 participants.

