### Interim analyses {21b}

If recruitment is not achievable in more than one center, an interim analysis of the achieved effect size and subsequent reanalyses of the required sample size will be performed to evaluate whether continuation of the trial is realistic.

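### As worded, the centre-exclusion rule sets a bar that at most two of the four centres can reach when recruitment is on schedule

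*Protocol article*

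**What the plan says.** The rule is in the protocol article under Criteria for discontinuing or modifying allocated interventions {11b}, in the part that deals with centres: "for participating centers: Recruitment and data assessment of the follow-up examinations will be monitored by the Data Safety and Monitoring Board". That part mentions recruitment milestones at several time-points, which the article does not list, and then sets the exclusion rule: "If recruitment at the 50% landmark is below 20% of the total targeted number of patients, the enrolling center will have to be excluded". The wording is mandatory.

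Study setting {9} fixes the number of centres: "The study will be carried out in four physiotherapy practices in Germany".

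Two recruitment totals appear, both for the whole trial. Sample size {14} says "the total number of participants to be recruited is 104 participants". The abstract says "A total of 90 participants aged 18 to 90 with chronic musculoskeletal disorders will be randomized". The article states no target for any single centre.

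A separate whole-trial provision, in {11b} and again in Interim analyses {21b}, begins "If recruitment is not achievable in more than one center, an interim analysis". It leads to a look at the achieved effect size and a re-calculation of the sample size.

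**The concern.** The rule judges one centre at a time, but on its plain wording it measures that centre against the total for all centres. With four centres, an equal share of half the target is 12.5% of the total, already well under 20%. A centre recruiting exactly its share would therefore be excluded.

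If the rule is followed, an on-schedule trial loses at least half its sites at mid-recruitment. Centre is the stratification factor in the randomisation {16a} and a fixed factor in the primary ANCOVA {20a}, so closures also bear on the data that the analysis will have. If the rule is set aside because it is unworkable, closing a centre becomes an ad hoc decision, which pre-defined milestones are meant to prevent.

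**Working it through.** **Inputs**
- Threshold: 20% of the total target, checked at the 50% landmark ({11b}).
- Centres: 4 ({9}).
- Total target N: 104 ({14}) or 90 (abstract).

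**The plan's own total.** The sample size section says "30 participants in each group (guided meditation, aromatherapy, and control) are required", so 3 × 30 = 90, and "We anticipate a drop-out rate of 15% during the follow-up period". Then 90 × 1.15 = 103.5, rounded up to 104, which is the stated figure. Dividing by the retained fraction gives 90/0.85 = 105.9, rounded up to 106. The check below therefore covers 90, 104 and 106.

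**Formulas**
- Patients a centre needs: 0.20 × N, rounded up.
- Patients enrolled over all centres at the landmark, on schedule: 0.50 × N.
- Most centres that can pass: 0.50 × N divided by the number needed, rounded down.

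| N | Needed per centre | Enrolled in all | Equal share of 4 | Most that can pass | Needed for 3 to pass | Needed for 4 to pass |
|---|---|---|---|---|---|---|
| 90 | 18 | 45 | 11.25 | 45/18 = 2.5, so 2 | 54 (60% of N) | 72 (80%) |
| 104 | 20.8, so 21 | 52 | 13 | 52/21 = 2.5, so 2 | 63 (61%) | 84 (81%) |
| 106 | 21.2, so 22 | 53 | 13.25 | 53/22 = 2.4, so 2 | 66 (62%) | 88 (83%) |

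Listing every way to divide 45 or 52 patients over four centres confirms a maximum of two passing centres. The choice of N does not matter, because 0.50/0.20 = 2.5 for any total. With equal recruitment each centre holds 12.5% of the total and none passes.

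**If the landmark is a date.** With recruitment on schedule at half the recruitment period, the same counts apply. Three centres could pass only if about 60% of the target were already enrolled by then, and four only at about 80%.

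**If the denominator is the centre's own target.** For illustration only, assume equal targets of 104/4 = 26. Then 20% is 5.2 patients, against 13 expected on schedule, and all four centres can pass.

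**The case against.** The strongest reply is that the sentence is ambiguous rather than wrong. It sits among the provisions for centres and judges the enrolling centre, so the total could mean that centre's own total, as opposed to its count at the halfway point. Nothing in the sentence ties the figure explicitly to the whole trial. The article also condenses a fuller protocol, which may list the milestones and centre targets. This has weight: the authors may well have meant the centre's own target, and the absence of centre targets from an article is not itself a fault. But the rule is stated here, it is mandatory, and the only totals that the reader can apply to it are the trial's. A likely intention is a reason to correct the sentence; it does not make the sentence clear.

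A second reply is that the landmark may be a time-point. That stands as a limit: the ceiling of two centres holds for a trial on schedule, not for one well ahead of it.

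A reader might also infer more than the documents support:
- *That centres would be closed whatever their performance.* Performance still decides which centres pass: two centres with 26 of the 52 patients each would both stay.
- *That the trial could not reach its target.* The article sets no cap per centre, so remaining centres could go on recruiting. The inference holds only if all four are excluded.
- *That the effect-size interim analysis would follow automatically.* Its condition is that recruitment is not achievable in two or more centres. Closing two centres could plausibly meet it, but the text does not equate the two.
- *That excluded centres' patients would drop out of the analysis.* The rule does not say so, and the article commits to an intention-to-treat analysis.

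Finally, this is a site-management rule. It leaves the primary endpoint, the model and the significance level unchanged, which limits its weight.

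**Conclusion.** The point holds for the rule as worded. With a per-centre count, a trial-wide denominator, four centres and on-schedule recruitment, at least two of the four centres are excluded, and all four if recruitment is balanced. This is a stated decision threshold in conflict with the trial's own design, not a missing detail. The arithmetic is certain on that reading; whether the authors intended that reading is not. If they meant each centre's own target, only the wording is at fault. Either way the sentence should be corrected before the landmark is reached.

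**What to change.** Restate the threshold as a percentage of each centre's own recruitment target, and state the four targets. They need not be equal, but they should add up to the trial's recruitment target, for which the abstract and the sample size section now give different figures. Say whether the 50% landmark is the point at which half the patients have been enrolled or at which half the recruitment period has passed. It would also help to say whether excluding a centre under this rule counts towards the condition for the interim analysis in {11b} and {21b}.

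The change is one or two sentences and four numbers, and costs no patients or data. Under the article's section on amendments {25} it needs ethics committee approval and authorisation by the study team and the DSMB. As worded, that section also calls for updated consent forms to be signed again after any modification, so this change is best bundled with other corrections.

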### Strategies to improve adherence to interventions {11c}

For the total duration of the trial, a telephone line will be opened up, and patients are encouraged to call any time in case that questions regarding the trial procedure occur. Further, to enhance confidentiality, relatives of all participating patients will have the possibility to take part in a training course on meditation and aromatherapy.

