### Relevant concomitant care permitted or prohibited during the trial {11d}

This trial does not prohibit other treatments.

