## Statistical methods

### Statistical methods for primary and secondary outcomes {20a}

#### Primary estimand

The point estimates for both treatment arms will be presented as mean and standard deviation accompanied by the corresponding 97.5% confidence interval and will be compared between the meditation, the aromatherapy intervention and standard of care. To test the null hypothesis H_0_: μ_diff_ = 0 at a two-sided significance level of 0.025, an analysis of covariance (ANCOVA) with the respective component score at month 6 as dependent variable, treatment arm and center as fixed factor, and pain score at baseline, sex, and age as additional covariates will be used. Results will be presented using estimated marginal means of the difference between both groups accompanied by corresponding 97.5% confidence intervals. The study will be considered as successful if at least one component score shows a significant difference between both treatment arms. Two-sided alpha will be set at 0.025 to adjust for multiple testing.

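### The adherence section offers training in both tested techniques to relatives in every arm, standard care included, which opens an avoidable route to cross-arm use before the month-6 analysis

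*Protocol article*

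**What the plan says.** All references are to the protocol article.

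- **Strategies to improve adherence to interventions {11c}:** "relatives of all participating patients will have the possibility to take part in a training course on meditation and aromatherapy". The sentence gives enhancing confidentiality as the purpose. It names no arm and no timing.
- **Group 3: Control (standard of care), in {11a}:** "The control group will receive standard care as per existing clinical guidelines".
- **Explanation for the choice of comparators {6b}:** "The inclusion of a standard care group allows us to evaluate the added value of the psychosomatic interventions (meditation and aromatherapy) beyond conventional treatments".
- **Primary estimand {20a}:** outcomes "will be compared between the meditation, the aromatherapy intervention and standard of care", by ANCOVA on the month-6 score. The Abstract specifies an intention-to-treat approach.
- **Relevant concomitant care {11d}:** "This trial does not prohibit other treatments".
- **Eligibility {10}:** current structured mind-body practice is an exclusion ("yoga, meditation programs, relaxation therapy"), and complementary therapies must be "discontinued ≥ 2 weeks before enrollment".

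**The concern.** A standard-care participant has no study technique to adhere to, so an adherence measure has no purpose in that arm. Read literally, the sentence still lets the trial train that participant's family in both techniques. It also trains families in each active arm in the technique their relative was not assigned.

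Both techniques are done at home and are easy to pass on: a 23-minute recording, and fragrance sticks used for a few minutes a day. If trained relatives pass them on, the arms become more alike, and an intention-to-treat analysis absorbs the whole of that loss. A null result would then be hard to read: the techniques may not work, or some controls may have been using them. The standard-care arm is there to isolate added value, and this is the property put at risk.

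**Working it through.** **Step 1. Is the route open in the text?** Four conditions decide this.

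1. *Who is offered the course?* The sentence covers all participants' relatives, so it includes controls.
2. *What is taught?* One course, "a training course on meditation and aromatherapy", covers both techniques and is not matched to allocation.
3. *When?* No timing is given. The phrase in {11c} about the total duration of the trial belongs to the telephone line, not to the course. Nothing defers the course past the month-6 analysis or the 12-month visit.
4. *Does anything block uptake?* {11d} prohibits nothing. The {10} exclusion and washout act only up to enrolment.

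The route is therefore open for standard care and between the active arms.

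**Step 2. Direction.** Suppose the techniques help.

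- Uptake by controls lowers the difference between that technique's arm and control.
- Crossing between the active arms lowers the difference between them.
- An active-arm participant who adds the other technique could instead raise that arm's difference from control. For this one path the net direction is not fixed.

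**Step 3. Size, under an assumed loss.** Inputs from Sample size {14}: effect size 0.5 between intervention and control (read here as a standardised mean difference d; the metric is not stated), and 30 per group. The lost share c is assumed, because the documents give no figure.

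- Diluted effect: d′ = 0.5(1 − c).
- Required n is proportional to 1/d², so it grows by 1/(1 − c)².
- If a share p of controls takes up the technique and gets a fraction e of its effect, then c = p × e. For example, 20% uptake at half effect gives c = 0.20 × 0.5 = 10%.

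| Assumed c | d′ | 1/(1 − c)² | Plan's 30 per group scaled |
|---|---|---|---|
| 0 | 0.50 | 1.00 | 30 |
| 10% | 0.45 | 1/0.81 = 1.23 | 30/0.81 = 37.04, so 38 |
| 20% | 0.40 | 1/0.64 = 1.56 | 30/0.64 = 46.9, so 47 |
| 30% | 0.35 | 1/0.49 = 2.04 | 30/0.49 = 61.2, so 62 |

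The last column takes the plan's 30 per group as adequate at c = 0.

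**Step 4. What the factor depends on.** The plan's 30 per group does not reproduce from its stated inputs. An unadjusted comparison at d = 0.5, two-sided alpha 0.05 and 80% power needs 63 per arm. Thirty would need a baseline correlation of about 0.72, which is not stated. That is a separate matter. Alpha, power and the covariate gain scale n equally at every c, so they cancel from 1/(1 − c)².

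Absolute power does not have this property. At 30 per arm, d = 0.5, alpha 0.025 and c = 0, it is about 36% for an unadjusted t-test. It is about 48% or 66% if the baseline correlation is assumed to be 0.5 or 0.7. Power figures would therefore mix this point with the sample-size problem, so the conclusion uses only the factor.

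**The case against.** The strongest reply is that nothing shows contamination will happen. The course is optional and goes to relatives. A relative must attend, pass the technique on, and the participant must then practise it. The body-scan recording is on a web page whose address the article prints, so the course may not be the only access. The sticks are described as supplied to Group 2, and nothing says the course hands them out. The misfit of the stated purpose suggests a drafting slip rather than a deliberate plan.

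Most of this stands, and it limits the point to an open route of unknown size. It does not remove the point. Public access to a recording differs from the trial itself offering instruction to control households, and a drafting slip is a reason to correct the sentence.

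Three stronger readings are tempting and are not supported.

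- *The standard-care arm is contaminated.* The documents give neither uptake nor timing, so this cannot be inferred.
- *{10} and {11d} contradict each other.* One governs entry and the other governs care afterwards. Both can hold together, and the exclusion criterion does not name aromatherapy.
- *Controls' expectations will be distorted by the course.* Participants already receive a verbal and written explanation of the study, and the Discussion already concedes expectancy effects. The documents do not show what a relative's course would add.

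It is also fair to say that recording of cross-use may exist in an eCRF that is not shown. The fix is worded with that in mind.

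**Conclusion.** The point holds as a design weakness in one sentence. As written, {11c} has the trial offer both tested techniques to families in every arm during follow-up, and nothing in the article restricts the resulting use. Any uptake by controls would bias the contrasts with standard care toward no difference, so the main threat is a missed or understated effect rather than a false benefit. This direction assumes that the techniques help and that control uptake outweighs any added technique in the active arms.

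The size is illustrative only: 1.23 to 2.04 times the sample for an assumed loss of 10% to 30% of the contrast. The true loss may be smaller, including none. The plan should change because the exposure is avoidable at little cost, not because a particular loss has been shown.

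**What to change.** In {11c}:

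1. Limit the course to relatives of participants allocated to a technique, and teach only that technique.
2. Offer it to relatives of standard-care participants after their 12-month visit.
3. Replace the stated purpose. Confidentiality does not fit a measure listed under adherence, and the sentence should say what the course is for.

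In data collection, record use of meditation and aromatherapy in all three arms at each visit, if the eCRF does not already do so. Any cross-use can then be described beside the intention-to-treat result.

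This point needs no change to {11d} or to the entry criteria. The cost is a short amendment to one passage and, at most, one added eCRF question. The downside is that relatives of standard-care participants wait until follow-up ends.
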